## Abstract

**Background:**

A primary concern within the healthcare system is to make treatment more accessible as well as attractive for the great majority of alcohol-dependent people who feel reluctant to participate in the treatment programs available. This paper presents the protocol for a randomized controlled trial (RCT) to test the efficacy of two different technical devices (mobile phone application and breathalyzer) on alcohol consumption.

**Methods:**

The study is a three-armed RCT with follow-ups 3 and 6 months after randomization. In total, 375 adults (age 18+ years) diagnosed with alcohol use disorder (AUD) will be invited to participate in a 3-month intervention. The primary outcome is the number of days with heavy drinking, defined as four or more standard drinks (12 g alcohol/drink) and measured by the timeline follow back (TLFB) and Alcohol Use Disorder Identification Test (AUDIT) instruments at 3-month and 6-month follow-up. Secondary outcome measures include weekly alcohol consumption, measured by the TLFB, AUDIT, and phosphatidylethanol in blood values at 3-month and 6-month follow-up (number of days with blood alcohol concentration levels exceeding 60 mg/100 ml).

**Discussion:**

Improving ways of collecting data on alcohol consumption, as well as the treatment system with regards to AUD, is of vital importance. Mobile phone technology, with associated applications, is widely recognized as a potentially powerful tool in the prevention and management of disease. This study will provide unique knowledge regarding the use of new technology as instruments for measuring alcohol consumption and, also, as a possible way to decrease it.

**Trial registration:**

ISRCTN, ISRCTN14515753. Registered on 31 May 2018.

**Electronic supplementary material:**

The online version of this article (10.1186/s13063-018-3137-y) contains supplementary material, which is available to authorized users.

## Background

It is well known that alcohol causes significant morbidity and mortality [1]. Approximately 70 diseases have been estimated to be wholly or partly caused by alcohol [2]; for example, cardiovascular diseases, cancers, infectious diseases, neurological diseases, and mental disorders—including alcohol use disorder (AUD). AUD is a disease where at least three out of six ICD-10 criteria should have occurred together for at least 1 month or, if persisting for periods of less than 1 month, should have occurred together repeatedly within a 12-month period. The criteria include a strong *desire* to drink alcohol, *impaired* capacity to *control* alcohol-taking, *preoccupation* with alcohol use, *persistent* substance use *despite* clear evidence of *harmful* consequences, a physiological *withdrawal state*, and evidence of *tolerance*.

Most people with alcohol use disorder do not seek treatment [3, 4]. Different studies estimate that fewer than 20% have ever been in treatment [5, 6]. Available treatment in specialized addiction clinics is perceived as unattractive and stigmatizing, and it appears that it is only when problems become very severe that the barriers to treatment are overcome [7].

Thus, a primary concern within the healthcare system is to make treatment more accessible as well as attractive for the great majority of alcohol-dependent people who feel reluctant to participate in the traditional treatment programs available.

In recent years, a number of technical devices have been developed for this particular purpose; for example, web-based preventative and treatment self-help programs aiming at reducing alcohol use and/or treating AUD [8]. Internet-based interventions are typically well received by clients and may attract individuals who would otherwise not seek help, but prior research on their effectiveness is inconsistent [9]. Moreover, and even more recent, mobile phone technology is getting widely recognized as a potentially powerful tool for the prevention and management of disease [10]. Increased accessibility, real-time and ecological assessments, as well as high allowance for collecting sensitive information are some of the advantages of smartphone applications. There is, however, little research to provide evidence of their putative effectiveness [11, 12].

So far, mobile technology and health-related apps have been evaluated with regards to diabetes, infectious disease (HIV, tuberculosis), dermatology (psoriasis), and smoking [13–17]. Studies on the topic have also been made within the field of mental health, including depression, sleep disturbances, anxiety, and self-harm [18]. To our knowledge, there are only two previously published studies regarding tests of apps in the treatment of alcohol use disorder; the Location-Based Monitoring and Intervention for Alcohol Use Disorders (LBMI-A) and the Addiction—Comprehensive Health Enhancement Support System (A-CHESS). The LBMI-A app has features intended to provide support, and in a study population of 28 individuals with an alcohol use disorder the tool for monitoring consumption was appreciated [19]. For the other app, A-CHESS, results from a randomized controlled trial of 349 individuals showed that patients using the app (*n* = 170) reported less risky drinking than the controls (*n* = 179) [20]. The main criticism regarding previous research in this area concerns sample size, high risk of bias, and lack of studies considering long-term follow-up [12, 18].

In this project we aim to examine two mobile phone applications (apps), “Glasklart” and the combination of a portable breathalyzer with a mobile phone application “iBAC”, in the treatment of AUD. The Glasklart app enables the user to make instant, continuous, and anonymous registration of the alcohol volume (i.e. standard drinks) consumed on each occasion, with the possibility to also share information with a caregiver. The advantages of using a smartphone app are several; smartphones may store and share data in real time, give geographical location, allow for on-demand communication, are almost always on, and are portable [21]. The iBAC device gives a biologic measure of the current blood alcohol concentration (BAC). The advantage is that this provides an estimate that is independent of self-report and that this device is also easily managed using a mobile phone. In general, alcohol consumption data are collected in retrospect, thus increasing the risk of recall bias [22]. Possible consequences of incorrect information regarding alcohol consumption are several; for example, difficulties in clinically assessing alcohol-related problems and evaluating treatment of alcohol-related problems for the individual, and difficulties in examining the health effects of alcohol consumption. This project enables *instant* assessment of alcohol consumption which in turn may allow for more accurate reports.

We will conduct a randomized controlled trial (RCT) to examine the effects of using apps as complements to standard treatment on alcohol consumption in adults with AUD. A comparison group will receive standard treatment only, described later. Specifically, we aim to validate Glasklart and iBAC as instruments for assessing alcohol consumption, and to investigate whether assessment (self-monitoring), using Glasklart or iBAC, has a reducing effect on alcohol consumption.

### Key research questions

Do mobile phone applications provide better (i.e., higher) estimates of alcohol consumption than current measurement methods?Does the use of these devices, on the one hand featuring self-monitoring of alcohol consumption, and on the other measuring blood alcohol levels through a breathalyzer connected to a mobile phone, have an effect on the user’s alcohol consumption?How are Glasklart and iBAC perceived by the users? This question includes assessments of the technical components, such as app features including reminders, geolocalization, and registration of mood (qualitative study).

## Methods

This study will be conducted and reported in accordance with the Standard Protocol Items: Recommendations for Interventional Trials (SPIRIT) guidelines (see Fig. 1 and Additional file 1 for the SPIRIT figure and checklist, respectively).

**Fig. 1 Fig1:**
[figure not shown]
Standard Protocol Items: Recommendations for Interventional Trials (SPIRIT) figure. AUDIT Alcohol Use Disorder Identification Test, ICD-10 International Statistical Classification of Diseases and Related Health Problems 10th revision, PEth phosphatidylethanol, SF-12 12-item Short form Health Survey, TAU treatment as usual, TLFB timeline follow back

### Setting and participants

The study will be conducted at Riddargatan 1: Center for Alcohol and Health, an outpatient treatment clinic located in central Stockholm specializing in AUDs. The clinic opened in 2011 and is staffed by physicians, psychologists, and allied health workers with expertise in the treatment and management of addictive behaviors, including AUDs. The target group at Riddargatan 1 is people with alcohol dependence but no major psychosocial problems.

#### Inclusion/exclusion

Inclusion criteria were fulfilling diagnostic criteria for alcohol dependence according to ICD-10 and age 18 years or older.

Exclusion criteria were severe physical or mental disorder, pregnancy, currently undergoing other treatment for alcohol problems, and recent treatment for severe alcohol problems (e.g., alcohol withdrawal).

### Study design and randomization

The study comprises three parts:A randomized controlled trial, measuring the effect on alcohol consumption of adding the two devices Glasklart and iBAC to treatment as usual (TAU) at Riddargatan 1.A validation study of Glasklart and iBAC.A qualitative study, where focus groups and semi-structured interviews will be used to study participants’ perceptions of these technological tools.

#### Randomization

Following the first treatment session, the counselor informs the study coordinator about the new study participant (see Fig 2 for participation flow diagram). The coordinator records baseline data in a study database and initiates the randomization procedure. This procedure is conducted by an administrator with no other role in this study. Randomization is done by a computer program, where participants are randomized (in blocks of 10) either to treatment as usual (TAU), or TAU + Glasklart, or TAU + iBAC. TAU in this study at Riddargatan 1 involves pharmacotherapy in combination with manualized psychological treatment—either the “Guide to better drinking habits”, building on theories on guided self-change [23–25], or the “Guide to Controlled drinking”, referring to theories on behavioral self-control training [26]. Each study participant is given a study number (1–375). Only the administrator has access to the code key, where the study number is coupled with the participant’s person number. The code key is stored in a locked cabinet in the patient archive at the clinic.

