#### Blinding

A team of psychiatric nurses at the clinic will be trained to conduct patient assessments before, during, and after treatment. Assessors will be aware of the patient’s treatment allocation. Genuine blinding of assessors is not feasible given the technical devices that need to be displayed in the project. Thus, blinding will not be possible at the patient or therapist level. At the analysis stage, however, the participants’ identity will not be known to the researcher; that is, all data will be available according to group allocation (1, 2, or 3).

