### Statistical analyses and power calculation

The sample size has been estimated from the primary outcome variable, heavy drinking days during the past 30 days before baseline, at 3 months and at 6 months after baseline. Based on the assumption that the effect size of the intervention will be in the range of 0.4 SD in groupwise comparisons (alpha 5% and two-tailed tests) we need at least 98 individuals in each of the three treatment arms, and given an expected 25% dropout rate this motivates our choice of *N* = 375.

Data will be analyzed according to intention to treat (ITT). A secondary analysis will be per protocol for those participants who have contributed data at baseline and at 3-month follow-up. Primary and secondary outcome measures will be analyzed through ANOVA for repeated measures, with time (baseline, 3 months, and 6 months) as the dependent variable and type of intervention (TAU, or TAU + Glasklart, or TAU+ iBAC) as the independent variable.

A multiple regression analysis will be performed to investigate the extent to which the different predictor variables (consumption level and pattern, severity of dependence) contribute to the variation in the primary and secondary outcome measures.

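### A block size of 10 cannot be balanced across three arms, and the article gives no rule for the tenth place; the block size should be a multiple of 3.

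*Protocol article*

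**What the plan says.** The Abstract describes the design: "The study is a three-armed RCT with follow-ups 3 and 6 months after randomization". It gives the total as follows: "In total, 375 adults (age 18+ years) diagnosed with alcohol use disorder (AUD) will be invited to participate".

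Under Randomization, "participants are randomized (in blocks of 10) either to treatment as usual (TAU), or TAU + Glasklart, or TAU + iBAC". The allocation is generated by computer and run by an administrator who has no other role in the study. The article states neither an allocation ratio nor the composition of a block.

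Under Statistical analyses and power calculation, the assumption is that "the effect size of the intervention will be in the range of 0.4 SD in groupwise comparisons", with "alpha 5% and two-tailed tests". From this it concludes that "we need at least 98 individuals in each of the three treatment arms". An expected dropout of 25% then leads to N = 375.

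Under Blinding, the article says that "blinding will not be possible at the patient or therapist level", and that assessors will know the allocation. Setting and participants names a single outpatient clinic.

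**The concern.** Permuted blocks are used so that the arms are level at the end of each block. With three arms and an intended ratio of 1:1:1, that requires a block size that is a multiple of 3. The stated size is 10, so each block must give at least one arm more places than another. The article does not say which arm, or how that is decided.

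Equal arms are implied, not stated. One per-arm minimum applies to all three arms, 375 divides exactly into 3 × 125, and nothing in the article suggests an unequal ratio. The stated block size and the implied allocation therefore do not fit together.

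At stake is the balance of the arms, and through it the power of the comparison between the two smallest arms. A lesser matter is predictability: a single published block size, in an open-label trial at one clinic, makes it easier to guess later allocations from earlier ones.

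**Working it through.** **Inputs.** Block size 10 (Randomization). Three arms and N = 375 (Abstract). Difference 0.4 SD, two-sided 5%, 98 per arm, 25% dropout (Statistical analyses and power calculation). Power is not stated; 80% is assumed because it reproduces the 98.

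**The plan's own figure.** n per arm = 2 × (1.960 + 0.842)² / 0.4² = 2 × 7.85 / 0.16 = 98.1, which matches 98. The exact t-test value is 99.1, and at 98 per arm the t-test has 79.6% power. The per-arm requirement is therefore reproduced, for pairwise comparisons of equal arms.

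**Block arithmetic.** 10 = 3 × 3 + 1, so the closest split of one block is 4:3:3. 375 = 37 × 10 + 5, that is 37 full blocks and 5 patients in a last partial block.

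**Reference case: equal arms.** 375 / 3 = 125 randomized per arm, and 125 × 0.75 = 93.75 evaluable. Two-sample t-test power at 0.4 SD is 77.8%.

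The effect of the block size depends on the unstated rule for the extra place. Three rules cover the plausible cases.

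**(a) The same arm always takes it.** Expected arms are 375 × 0.4 = 150 and 375 × 0.3 = 112.5 twice. After dropout: 150 × 0.75 = 112.5 and 112.5 × 0.75 = 84.4 twice.

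**(b) It is drawn at random in each block.** In 50,000 simulated sequences (37 full blocks plus 5 patients from a further block), the gap between largest and smallest arm had median 6 and 95th percentile 12. The smallest arm had 119 or more in about 95% of runs. Power between the two smallest arms was 77.3% at the median and 76.7% at the 5th percentile.

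**(c) It rotates.** Every 30 patients are exactly 10/10/10. After 36 blocks each arm has 120, block 37 makes it 124/123/123, and the last 5 patients leave every arm between 123 and 127. For 123 against 125, power is 77.4%.

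| Rule for the extra place | Randomized | Power, two smallest arms | Power, largest v smallest |
|---|---|---|---|
| Equal arms (reference) | 125/125/125 | 77.8% | 77.8% |
| (a) Same arm always | about 150/112/112 | 73.3% | 78.9% |
| (b) Random per block | smallest 119 or more in 95% of runs | 77.3% (median) | 77.7% (131 v 119) |
| (c) Rotating | each arm 123 to 127 | 77.4% (123 v 125) | not below the two smallest |

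The loss for the weakest comparison is 77.8 − 73.3 = 4.5 points under (a), 77.8 − 77.3 = 0.5 points at the median and 77.8 − 76.7 = 1.1 points at the 5th percentile under (b), and 77.8 − 77.4 = 0.4 points in the case shown under (c).

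**The case against.** The strongest reply is that the article does not describe how a block is composed, and that a condensed article may leave this to a full protocol or randomization plan. The ratio of 1:1:1 is also inferred, and the 98 is a minimum. Under a rotating or random extra place the arms end near equal. Even under a fixed 4:3:3, larger versus smaller has slightly more power than equal arms give (78.9% against 77.8%). If TAU were the larger arm, both device-versus-TAU comparisons would lose nothing.

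Most of this stands, and it limits the size of the point. It does not remove it: the article states a specific parameter, and that parameter does not fit the number of arms.

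A reader might be tempted by four stronger readings, which the document does not support.

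- *The scheme cannot give equal arms.* It can. Rules (b) and (c) give equal or nearly equal totals; only single blocks are necessarily unbalanced. A fixed 4:3:3 composition is an assumption that the article nowhere states.
- *The block size causes the shortfall below 98.* Equal arms already leave 93.75 evaluable. That comes from the dropout inflation: 98 × 1.25 = 122.5 per arm is close to the 125 used, whereas 98 / 0.75 = 130.7 would be needed. It is a separate issue.
- *375 should be a multiple of 10.* An incomplete last block is routine and is not a defect.
- *Concealment is broken.* Randomization follows eligibility assessment, inclusion and the recording of baseline data, and is run by an independent administrator. To predict an allocation, staff would need the block boundaries, all earlier allocations and the composition rule, and the article does not show that they have these. What remains is that a single published block size in an open-label single-clinic trial is a good reason to vary the sizes and withhold them.

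**Conclusion.** The point holds in a limited form. Blocks of 10 cannot be balanced across three arms, which conflicts with the equal allocation that 98 per arm and N = 375 = 3 × 125 imply, and the rule for the tenth place is not given. The block size itself introduces no expected bias.

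The cost in power is about one point or less if the extra place rotates or is random. It is about 4.5 points (73.3% against 77.8%), for one of the three pairwise comparisons, if one arm always takes it. These figures assume 0.4 SD, two-sided 5%, 25% dropout spread equally over the arms, and a t-test for each pair. The simulated figures also assume that the last 5 patients come from an ordinary 4:3:3 block.

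This should be fixed because the stated parameter is inconsistent with the design and correcting it is cheap. It is not a fault that would undermine the trial's conclusions.

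**What to change.** State that allocation is 1:1:1, and replace the block size of 10 with sizes that are multiples of 3. Sizes that vary at random, for example 6 and 9, are preferable, kept out of any document available to clinic staff because the trial is open-label at one clinic. A single size of 15 would divide 375 exactly (25 blocks, 125 per arm), but it would keep the weakness of a fixed size. If the intended meaning was 10 per arm, correct the text to blocks of 30. If an unequal ratio was intended, state it and redo the sample size for it.

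The cost is one parameter in the randomization program and one sentence in the protocol, provided the change is made before recruitment. If patients have already been allocated, report the rule that was actually used and apply the new sizes from a stated point onward.

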**Fig. 2 Fig2:**
[figure not shown]
Participant flow diagram. AUD alcohol use disorder, AUDIT Alcohol Use Disorder Identification Test, ICD 10 International Statistical Classification of Diseases and Related Health Problems 10th revision, ITT intention to treat, TAU treatment as usual, TLFB timeline follow back

At the second treatment session, the counselor collects the signed informed consent document. The counselors then explain and demonstrate the two devices: Glasklart and iBAC. Each patient randomized to the iBAC intervention is provided with an iBAC breathalyzer (one of the smallest breathalyzers available) for the duration of the study. The apps (Glasklart and iBAC respectively) will be installed on the participants’ smartphones. The iBAC breathalyzer is linked to the mobile phone via Bluetooth and the information on the BAC level is saved in the breathalyzer and mobile app. The user identifies herself or himself using a color-coding photographic function to verify that the intended user takes the test.

Patients randomized to Glasklart will be instructed to register every glass of alcohol they drink in the Glasklart app. They will receive automatic reminders, a so-called push notification that pops up on the mobile device after half an hour (after first registration), to continue registration if they have consumed more alcohol (i.e., “do you have anything more to register?”). Patients randomized to iBAC treatment will also receive a message on their mobile phone instructing them to use their iBAC breathalyzer at hourly intervals during drinking occasions, as long as these go on. That is, the iBAC is programmed to contact the patient with push notification according to a preset time schedule. The patients can then review their drinking through the apps respectively. Glasklart will describe the number of drinks consumed, when and where, in what mood, and whether alone or together with others. iBAC will describe the BAC level at different time points. Both of these devices can be viewed on a daily, weekly, or monthly basis. Moreover, the information collected is also visible for the counselors.

At all sessions of the treatment program, at baseline, at 3 months, and at a follow-up after 6 months, the timeline follow back (TLFB) and AUDIT will be recorded, and blood tests will be analyzed for phosphatidylethanol in blood (PEth).

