### Procedure

Recruitment will be done at Riddargatan 1, where people starting a treatment program for alcohol dependence will be informed about the study by the physician in charge. Patients expressing willingness to participate will be included. Information about the devices under study and the study procedures is provided by the counselor in charge of the treatment at the first treatment session, after assessing inclusion and exclusion criteria. Recruitment will also occur through advertisements placed in the waiting room.

To improve adherence, data on participant use of the devices will be continuously monitored. If necessary, the study coordinator will send reminders via text messages to the participants. Also, the devices will generate reminders (e.g., “push notifications”) for the participants.

When participants are included in the study they will be given timings for follow-up meetings at 3 and 6 months after study baseline. The follow-up visits will be with the study coordinator. All study questionnaires will be stored in a Case Record Form (CRF). Between the study visits, all CRFs will be kept in a locked and secure data archive room.

The counselors involved in this study are all certified therapists, with relevant specialist training for the treatment programs chosen for this study; that is, pharmacological treatment combined with the “Guide to better drinking habits” or the “Guide to Controlled drinking”, both based on cognitive behavioral treatment. Medications that will be used in this study are naltrexone and acamprosate.

The project is planned to start in 2018. Participant recruitment is expected to be completed by the end of 2019. Follow-ups will be completed by July 2020. Results will be reported during the fall of 2020.

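### Randomisation is started after session 1, but the signed consent form is in hand only at session 2, so non-return of consent could depend on the allocated arm

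*Protocol article*

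**What the plan says.** The Randomization section of the protocol article gives the order of events. "Following the first treatment session, the counselor informs the study coordinator about the new study participant". Then: "The coordinator records baseline data in a study database and initiates the randomization procedure". An administrator with no other role in the study runs the allocation.

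The text below Fig. 2 describes the next visit: "At the second treatment session, the counselor collects the signed informed consent document". It continues: "The counselors then explain and demonstrate the two devices: Glasklart and iBAC". In the same paragraph the patients are already spoken of as allocated: "Each patient randomized to the iBAC intervention is provided with an iBAC breathalyzer".

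The Procedure section gives the condition for entry that applies before any of this: "Patients expressing willingness to participate will be included". It also says when the study is explained: "Information about the devices under study and the study procedures is provided by the counselor in charge of the treatment at the first treatment session".

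The Blinding section states: "Thus, blinding will not be possible at the patient or therapist level". The section on statistical analyses and power specifies an intention-to-treat analysis.

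**The concern.** In an open-label trial, the commitment to take part should be complete before the allocation exists. Here the written evidence of it arrives after randomisation has been initiated, at the visit where the allocated device is provided.

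Two things can follow. First, a patient who does not come to session 2, or does not hand in the form, has been randomised and entered in the study database without documented consent. Second, the chance of this may differ between arms. What the arms ask of patients is visibly different: no device, registering every glass, or breath tests at hourly intervals while drinking, with the collected information visible to the counselor. If people drop out at this step for reasons tied to their arm and are then left out of the analysis, the groups compared are no longer the groups randomised. A larger sample does not cure that, and analysis can repair it only in part.

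**Working it through.** **Order of events in the visible text**

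1. Session 1: devices and procedures are explained (Procedure).
2. After session 1: the counselor notifies the coordinator, who enters baseline data and initiates randomisation (Randomization).
3. Session 2: the signed form is collected, then the devices are explained, and the breathalyzer is given to those allocated to it (text below Fig. 2).

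No visible sentence requires the signed form before step 2. Because the device is handed over in step 3, the allocation must be available at the clinic by that visit.

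**The plan's own figure**

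Inputs from the section on statistical analyses and power: effect 0.4 SD, two-sided alpha 5%, 98 per arm, 25% dropout, N = 375, which is 125 per arm if the arms are equal. Power is not stated; 80% is assumed.

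n per arm = 2(1.96 + 0.8416)² / 0.4² = 98.1, or 99 when rounded up. The stated 98 is reproduced, with power at 98 per arm of Φ(0.4·√(98/2) − 1.96) = Φ(0.84) = 0.80.

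**Effect on power, for an assumed 5% lost at session 2**

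- Number lost: 375 × 0.05 = 18.75.
- Planned dropout only: 125 × 0.75 = 93.75 per arm; power = Φ(0.4·√(93.75/2) − 1.96) = 0.78.
- With the extra 5%: 125 × 0.95 × 0.75 = 89.1 per arm; power = Φ(0.4·√(89.1/2) − 1.96) = 0.76.

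The difference is about 2 percentage points. The step from 80% to 78% comes from how N was inflated for dropout. It is a separate matter and is not counted here.

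**Possible selection bias, all values assumed**

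Let a share r of one device arm refuse after allocation and be excluded, with no refusals under TAU. Let refusers be s SD worse than those who consent. The mean of the remaining device patients then lies r × s below the mean of the whole arm, so the bias is r × s, in favour of the device.

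| r | Bias, s = 0.5 to 1 | Share of the 0.4 SD design effect |
|---|---|---|
| 5% | 0.025 to 0.05 SD | 6 to 12.5% |
| 10% | 0.05 to 0.10 SD | 12.5 to 25% |
| 20% | 0.10 to 0.20 SD | 25 to 50% |

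The document gives no value for r or s, and the sign would reverse if refusers did better than consenters. The table shows scale only.

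**The case against.** The strongest reply is that collecting a signed form is not the same as obtaining consent. The form may have been signed at or soon after session 1, when the study is explained, and only returned at session 2. That reading fits every sentence. It does not change the fact that the form is in hand only after randomisation has been initiated, or that a patient who misses session 2 may never return it.

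A reader might infer that patients learn their arm and then decide whether to consent. The text does not say so. The form is collected before the devices are demonstrated, and nothing states when the allocation is released to counselor or patient. The lack of blinding described concerns treatment and assessment. Disclosure before consent is therefore possible, not shown.

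A reader might also infer that the data of those who do not return the form cannot be used, or that they use up some of the 375 study numbers. No passage says either. Intention to treat is stated in general terms, the baseline measures are routine at the clinic, and how such patients are counted may be set out in an analysis plan that is not shown.

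Fig. 2, which the Randomization section cites for the flow, is not visible, and the article condenses a fuller protocol. Either might give a different order. If so, it would conflict with the article's text, and the two would need to be reconciled.

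Finally, early losses between the two sessions may already be part of the 25% dropout, which is not defined. In that case even the 2-point loss of power overstates the effect.

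**Conclusion.** The point holds as a flaw in the stated sequence: entry into the database and the start of randomisation come before the signed form is in hand, and the form is collected at the visit where the allocated device is provided, without blinding. This leaves room for randomisation without documented consent and for arm-dependent non-return of consent, which would undermine the intention-to-treat comparison.

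The document does not show that bias occurs. The loss of power is minor, about 2 points under an assumed 5% extra loss. The selection bias could be larger, but its size rests wholly on assumed refusal rates and differences between refusers and consenters, and on those patients being excluded from the analysis. The conclusion depends on the article's text being the sequence actually followed.

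**What to change.** Require the counselor to confirm the signed form before the coordinator enters baseline data and requests randomisation. The natural place is at or after session 1, since study information is already given there. Disclose the arm to patient and counselor only after that confirmation. Keep everyone randomised in the intention-to-treat set as far as consent permits, and report any refusals after randomisation by arm in the participant flow.

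This mainly reorders existing steps. The cost is timing: for patients who need time to return the form, randomisation and device set-up come later, possibly after session 2. If the form arrives only at session 2, data entry and allocation must either fit within that session or wait until after it.
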